### Unexpected consequences

We wish to capture any unintended consequences through our process evaluation arm, especially via the open questions in each year of the study (appendices 1 and 2). Many implementations of IT-based change have unintended consequences [29]. Specifically, we will explore with process improvement practices any issues about calling in or recalling patients, and any adverse reactions to therapy or interactions; we will also look at the rates of collection of prescriptions for ACEI and ARB as a proxy for medicine possession ratio. Quality improvement strategies based on open sharing of data may also have unintended consequences [30-32]; though in this study our data sharing is largely within the peer group rather than with the public.

### Data quality assurance

The study has been designed and will be reported in accordance with the CONSORT (Consolidated Statement of Reporting Trials) and its extension to cluster randomised trials [33]. Data will be controlled in accordance with data protection legislation, institutional protocols of St. George's University of London, and NHS policies for research and information governance for ensuring patient confidentiality [34]. Data will be analysed in SPSS (Statistical Package for Social Sciences) version 15 using an intention to treat approach.

### Biomedical data

These data will be extracted from general practice computer systems using the department of health sponsored data extraction system MIQUEST. MIQUEST has been developed by the NHS and is used in the national data quality programme at PRIMIS (Primary Care Information Services) [35]. This application allows identical searches on different brands of general practice computer systems. MIQUEST, when written in its 'remote' mode, extracts pseudo-anonymised clinical data. In its 'local' mode, it allows the extraction of patient identifiable data, such as postcodes for mapping onto multiple deprivation index, and for case-finding within the practice.

Routinely collected general practice computer data are complex and require significant processing and interpretation in order to obtain meaningful information [36]. The research team has considerable experience and has developed a published method [37]. The research data will be completely traceable due to the development of a sophisticated meta-data schema [38,29]. Our extraction technique includes thorough piloting and planning, and data processing with quality controls at each stage. All variables are examined for their distribution, and cleaned appropriately. Where possible, we use therapy and/or pathology tests to triangulate diagnostic and symptom codes.

An issue with routine data is that they are incomplete, and in contrast with other trial data are not systematically recorded at regular intervals. However, we expect to have relatively complete data on people with cardiovascular co-morbidity for the last five years (since the 2004 new contract for general practice) and hopefully longer. The quality of UK primary care data continues to increase, and there is a growing amount of published research that is based on routinely collected data – especially from countries with registration based primary care [14].

We have an agreement with CKD researchers in Galway, Ireland, who have experience of using routinely collected data to research CKD [39,40], that they will independently scrutinise our analysis procedures and generation of results tables.

### Economic evaluation

The Health Foundation is providing expert health economic consultancy to the quality improvement projects. Once our first-round data collection is complete, we will review this with the expert advisors [43].

### Questionnaire survey

A sample of 10 practices in three arms should enable us to compare changes in confidence in managing CKD. We expect to recruit practices with a mean practice list size of around 8,000 [46]. The latest workload survey suggested that 62% of GPs work full time [47]. There is approximately one GP per 1,700 patients. The confidence questionnaire adopts a five-point scale.

We estimate that there will be at least two practice nurses per 8,000 patients engaged in assessment of cardiovascular risk including management of CKD. We estimate an average of 10 practitioners per practice are eligible to complete the questionnaire and that we will achieve a >60% response rate, or 180 returned questionnaires.

A pilot study as part of the development of the questionnaire shows that the responses have a mean score of two, and standard deviation of about 1.26. We want to have a power of 0.80, or equivalently, the probability of a Type II error of 0.20, the sample size needed to show a change of 0.5 units in the five-point scale, the smallest individual change meaningful for the study, is 33 practitioners in each arm of the study.

### Stopping rules

Although negative effects are unlikely, any suspected negative effects will be investigated and the study suspended, pending review. The principal safety monitoring activities will be: the observation for falls in people newly started on additional BP lowering drugs; and to identify whether there is any relationship between systolic BP and rate of falls.

### Randomisation

#### Randomisation was conducted in blocks

Practices agree to participate in the study the basis that they will be assigned at random to an arm of the study. We excluded practices who wanted to choose an arm of the study. They are assigned their arm by simple random allocation. Randomisation will be performed with a table of random numbers by [name]; in the order practices complete their consent to participate. He allocates, at random, recruited practices in blocks of nine; accepting that there will be a final block of less than nine.

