**Methods:**

This three-armed CRT compares two well-established quality improvement interventions with usual practice. The two interventions comprise: provision of clinical practice guidelines with prompts and audit-based education.

The study population will be all individuals with CKD from general practices in eight localities across England. Randomisation will take place at the level of the general practices. The intended sample (three arms of 25 practices) powers the study to detect a 3 mmHg difference in systolic BP between the different quality improvement interventions. An additional 10 practices per arm will receive a questionnaire to measure any change in confidence in managing CKD. Follow up will take place over two years. Outcomes will be measured using anonymised routinely collected data extracted from practice computer systems. Our primary outcome measure will be reduction of systolic BP in people with CKD and hypertension at two years. Secondary outcomes will include biomedical outcomes and markers of quality, including practitioner confidence in managing CKD.

A small group of practices (n = 4) will take part in an in-depth process evaluation. We will use time series data to examine the natural history of CKD in the community. Finally, we will conduct an economic evaluation based on a comparison of the cost effectiveness of each intervention.

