#### Participants

The participants are GPs located in practices (our clusters) across England. We aim to recruit a nationally representative sample of practices from: in and around London – especially inner city and suburban southwest London; urban and rural Surrey and Sussex; Leicester city and surrounding areas; Birmingham inner city and suburban; and Cambridge. The locality structure is pragmatic because groups of practices need to come together for the ABE workshops. An inclusion criteria for a locality is that their local renal unit would support the workshop within their locality and review the GaP to minimise any conflict with local policy.

The primary research participants are GPs involved in the study who will receive the quality improvement interventions listed below. The interventions will be implemented at the practice (cluster) rather than the individual level. The study subjects (who may be regarded as secondary participants) will be all individuals with CKD within the study practices. CKD will be defined using the internationally accepted National Kidney Foundation (NKF) definition [23] using two measures of eGFR of less than 60 ml/min/1.73 m^2 ^at least three months apart. However, we will also explore the effects of including people with a single recording of eGFR.

The participants do not receive any financial incentives to participate, though they do receive financial compensation for the time actually spent attending study activities. These will vary according to the arm of the study they are allocated to.

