##### Distribution of clinical practice guidelines with prompts (GaP)

This is an established, low cost method of quality improvement [17]. It will provide a benchmark with which the effectiveness of the other quality improvement intervention can be compared. We will develop a consensus between the study team, our expert advisory group, and external peer reviewers, and produce appropriate guidance for the management of CKD in primary care. This guidance will be distributed to practices within this arm of the CRT (n = 25 practices plus 10 questionnaire practices) with six monthly updates and reminders. The guidance will be customised to fit with local practice and reflect guidance in that area. In addition practices will have access to a supportive website with information about CKD, frequently asked questions, and tools to improve CKD management.

The GaP documentation will typically be up to four sides of A4 paper stock, published in a glossy professionally printed form. It may be accompanied by local guidance or national brief guidance in the first intervention. We plan to distribute the NICE 'Quick Reference Guide' to managing CKD [24] as part of the second-year intervention.

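### Allocation is described as both simple and blocked by nine, and its single consent-order sequence does not balance the arms within the eight localities that shape the interventions

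*Protocol article*

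**What the plan says.** All quotations are from the protocol article.

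- **Method.** The subsection is headed "Randomisation was conducted in blocks". Its text says "They are assigned their arm by simple random allocation", and then "He allocates, at random, recruited practices in blocks of nine; accepting that there will be a final block of less than nine".
- **Order.** A table of random numbers is applied "in the order practices complete their consent to participate". One sequence is described, and no stratifying factor is named.
- **Locality.** The abstract's Methods paragraph refers to "general practices in eight localities across England". Under Participants: "The locality structure is pragmatic because groups of practices need to come together for the ABE workshops". The section on guidelines with prompts (GaP) states: "The guidance will be customised to fit with local practice and reflect guidance in that area". The inclusion criteria require the local renal unit to support the interventions, and the ABE section has a local renal specialist attend the workshops.
- **Numbers.** The core trial has 25 practices per arm (75). Another 10 per arm receive the questionnaire, which makes 35 per arm (105). The ABE section places both groups in the workshop arm.
- **Who knows what.** The Allocation concealment section deals with keeping the arm from the analysts. The Blinding section says that the field team know each practice's arm.

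**The concern.** Simple and blocked allocation cannot both be the method. Under the first, arm sizes are left to chance; under the second they are held nearly equal, as the sample size of 25 per arm presupposes. As written, the method can be neither reproduced nor reported correctly.

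The second issue is locality. Practices in one locality share a renal unit, local guidance and, in the ABE arm, a workshop built on comparison with the peers present. A single sequence in consent order balances the arms over the whole trial but not inside a locality. With only 25 core practices per arm, chance differences in locality mix add noise and can confound the comparison by chance. In an extreme case, a local workshop would have almost no peers to compare.

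The third issue is predictability. A fixed, known block size makes the end of a block easier to guess if whoever enrols practices knows the earlier allocations. The timing of consent could then be influenced.

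**Working it through.** **1. The plan's own sample size.** Inputs from the Sample size section: SD of practice means 3.77 mmHg, difference 3 mmHg, 5% level (two-sided assumed), power 80%.
n = 2 × (1.96 + 0.842)² × 3.77² / 3² = 24.8, so 25 per arm. The stated figure reproduces. Power at 25 is 80.3% by the normal approximation and 78.7% by the two-sample t test.

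**2. Simple against blocked.** With simple 1:1:1 allocation of 75 practices:
- SD of an arm's size = √(75 × 1/3 × 2/3) = 4.1 practices.
- P(25/25/25) = 75! / (25!³ × 3⁷⁵) = 0.011.
- P(largest arm minus smallest ≥ 5) is about 81% by simulation.

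With blocks of nine, 75 = 8 × 9 + 3 and 105 = 11 × 9 + 6. If each block, including the short last one, is split equally, the arms come out exactly equal. The two descriptions are therefore different designs.

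**3. Balance within localities under blocks of nine.** Simulation assumptions, none given in the article: eight localities of equal size (about 9 core practices, or 13 of all practices, each), three per arm in every block, and an equally split final block. Recruitment order is not stated, so two extremes are shown.

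| Chance that at least one locality has | 75, interleaved | 75, one run each | 105, interleaved | 105, one run each |
|---|---|---|---|---|
| an arm gap of 4 or more practices | 93% | 38% | 98% | 14% |
| 0 or 1 ABE practice | 68% | 26% | 22% | 0.1% |

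For workshop peers, 105 is the relevant count because questionnaire practices in the ABE arm also attend.

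**4. Predictability.** Assume three per arm per block, allocation one practice at a time, and earlier allocations and block size known to the recruiter.
- The 9th allocation is always determined.
- The 8th is determined when the last two belong to the same arm: 1/4 = 25%.
- The 7th is determined when the last three do: 3/84 = 3.6%.
- Always guessing the arm with most places left is right 4.79 times in 9, or 53%, against 33% by chance.

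If nine consented practices are drawn together, nothing can be guessed before consent.

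**5. What using locality could gain.** Let v be the share of between-practice variance explained by locality (assumption; no figure is given). With arms balanced within localities and locality in the model, the noncentrality is 3 / (3.77 × √(1 − v) × √(2/25)). Residual df = 75 − 3 − 7 = 65.

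| v | Power |
|---|---|
| 0 | 79.2% |
| 0.1 | 83.2% |
| 0.2 | 87.3% |
| 0.3 | 91.2% |

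Without locality (72 df) power is 79.3%, so if locality explains nothing the loss is about 0.1 percentage points.

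**The case against.** The contradiction may be one loose word. The subheading and the closing sentence both describe blocking, and simple may have been meant as unstratified. This stands: the chances under simple allocation show why the wording must be corrected, not what the trial is likely to have done.

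Unstratified blocked randomisation is valid, and chance imbalance across localities does not bias the estimate. This stands too. The power gain rests on an assumed variance share. The 30 sample practices may have contained little between-locality variation, and most of any gain comes from adjustment, which an analysis plan not shown here may already include.

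A reader might infer that allocations were predictable, or that concealment was broken. The article does not support that. It does not say that practices were allocated one at a time, that blocks held three per arm, or that recruiters knew earlier allocations. Allocation follows completed consent, practices had to accept any arm, and those wanting to choose were excluded. What remains is that the Allocation concealment section describes masking of analysts only.

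A reader might also infer that some ABE workshops would probably lack peers. Counting only the 75 core practices suggests this, but the workshops draw on all 35 ABE practices. The chance is then about 22% at most under the stated assumptions, and close to nil if localities were recruited in turn.

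Finally, the article refers to a completed first round of workshops, so at least some allocations had been made. This limits re-randomisation but not the correction of the text or the adjustment for locality.

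**Conclusion.** The concern holds in a limited form. The contradiction between simple and blocked allocation is certain, and blocking is the likelier intent. That the sequence is unstratified follows from the procedure as stated. Large arm gaps inside at least one locality are then close to certain if localities interleave (about 98% for 105 practices) and uncommon if each was recruited in one run (about 14%), given equal localities and three per arm per block. The consequence is lost precision and room for chance confounding, not bias. The 53% guessing rate is conditional and is not a finding that concealment failed. The sample size of 25 per arm is unaffected.

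**What to change.** 1. Delete the word simple and state one method: permuted blocks, their composition, and whether practices were drawn singly or in batches.
2. Keep all allocations already made. Randomise any remaining practices 1:1:1 within locality, in batches after consent, with the list held away from those who recruit, and report the change of scheme. State how earlier allocations were kept from recruiters.
3. Include locality as a fixed effect in the primary model. This applies even if allocation is complete, although adjustment without stratification recovers somewhat less than the power figures above when arms are uneven within localities.

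Cost: a text correction, a new list for whatever practices remain, some waiting until a locality batch is full, two allocation schemes within one trial, and 7 degrees of freedom (72 to 65), which costs about 0.1 percentage points of power if locality explains nothing.

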#### Allocation concealment

The allocation is not shared with those who will be involved in the data analysis. The clinical data collected are identical in all three arms of the study, so there should be no clues within these data as to which arm is which. The allocated arm is recorded in our database of practice details that is kept entirely separately from the pseudonymised table of data used for analysis. Within the analysis table the practices in each of the three arms are identifiable for analysis – but there is no labelling of which specific arm any practice is allocated to. Similarly, patient and practice identifiers are pseudonymised, which again makes it harder for the analysts to identify individual arms.

Ten practices in each arm are labelled as having had the questionnaire. The four in-depth process evaluation practices have a separate series of identification numbers so that they can have their data analysed but excluded from the study.

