##### Audit based-education (ABE)

In this arm, practices (n = 25 practices plus 10 questionnaire practices) will have a representative attend workshops. These practices will also have access to clinical practice guidelines provided to the second arm of the study. However, in addition, practices will receive three sets of detailed comparative feedback about their quality of CKD management at approximately nine-month intervals, and we will facilitate lists of patients needing interventions (local queries) being created within the practice. This comparative feedback about adherence to guidelines will be based on anonymised data collected from their general practice computer system prior to the ABE workshop.

The study will use an ABE model for quality improvement developed by the primary care data quality project that has been used in a variety of clinical contexts [19]. This involves feedback given in a workshop setting with at least one GP and one nurse or practice manager from each practice present. The workshops will be in two parts: the first will be facilitated by a GP familiar with the data, ideally from the locality, but if not, available from study team, and a local renal specialist in attendance to provide expert advice and information about local practice. The first part will be a presentation of the comparative adherence to evidence-based guidance for the management of CKD by the different practices present led by the GP. This section will highlight variation in the quality of care in a non-judgemental context. The second part of the meeting will be case studies, facilitated by the local consultant, which small groups will work through to explore dilemmas in management and how to overcome them.

The workshops are timetabled for two and a half hours of activity with additional break time to allow informal contact. Practices are expected to bring along at least one GP and one or two other members of the practice team: their practice manager and a nurse involved in cardiovascular risk assessment or diabetes within the practice.

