#### Blinding

The field team are aware of which practices are in which arm, because they must mail or invite participants to the relevant intervention. However, patient and practice details are pseudonymised. All cleaning and processing of data are carried out on the whole database (*i.e*., all three arms) simultaneously. We will do this by only revealing the arm allocation variable at the end of the study. We try to minimise access to signature data that would allow the arms of the study to be differentiated. (*e.g*., if an analyst knew the precise list size of one practice in the study.) However, we only plan to reveal this variable when it is needed for final comparison between arms.

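### The analyst blind is fragile as described: because the analysis table groups practices by arm, recognising one practice of known allocation exposes its whole arm

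*Protocol article*

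**What the plan says.** Under Allocation concealment the protocol article gives a general assurance, "The allocation is not shared with those who will be involved in the data analysis", and reasons that identical clinical data are collected in every arm, "so there should be no clues within these data as to which arm is which". It then describes the table itself: "Within the analysis table the practices in each of the three arms are identifiable for analysis", with the name of each arm withheld. The allocation is held in a database separate from this table, and patient and practice identifiers are pseudonymised.

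The Blinding section says that all arms are cleaned and processed together, and continues: "We will do this by only revealing the arm allocation variable at the end of the study". It recognises a risk of re-identification, "We try to minimise access to signature data that would allow the arms of the study to be differentiated", and gives an analyst's knowledge of one practice's exact list size as the example. It also says that the field team know the allocations, because they have to post materials or send invitations.

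Only the ABE arm is described as receiving practice-level results: "practices will receive three sets of detailed comparative feedback about their quality of CKD management at approximately nine-month intervals". These are built from anonymised data taken from practice systems before each workshop. Of the workshop's two parts, "the first will be facilitated by a GP familiar with the data", preferably a local one but otherwise from the study team. Three study-team members take part in the workshops.

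Appendix 3 lists list size, QOF performance and the number of practice members engaged in CKD management among the extracted practice data.

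**The concern.** Withholding the name of a group protects the analyst only while no member of that group can be recognised. Once practices share a group code, an analyst who recognises one practice and knows its allocation also knows the allocation of every other practice with that code.

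This matters more with routine records than in a trial with scheduled measurements, because several derivation choices are left to judgement. Biomedical data says that variables are examined and cleaned as appropriate. Participants and the secondary outcomes allow the CKD case definition to vary by date or number of eGFR readings. Appendix 1 lists both the latest blood pressure and a six-month mean as indicators. The Discussion discloses that some team members helped to develop ABE. A blind that lasts until these choices are fixed is the natural protection, and the article relies on one. If the blind were weaker than described, the trial report would also overstate it.

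**Working it through.** **Plan's own figure (background only).** With SD 3.77 mmHg, difference 3 mmHg, 5% level (two-sided assumed) and 80% power: n = 2 × (1.960 + 0.842)² × 3.77² / 3² = 24.8, so 25 practices per arm, as stated under Sample size. The point below does not depend on this.

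**Step 1: the two sections side by side.** Allocation concealment says that the table distinguishes the arms as groups without naming them. Blinding says that the arm variable is revealed at the end. The two agree if the table holds a masked code and the key is withheld, or if the code is added late. The article does not say which, and gives no date from which the grouping is present.

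**Step 2: the no-clues premise.** Collecting the same fields in every arm does not make their values uninformative. Blinding's own example of a signature is list size, and Appendix 3 lists it as extracted, with QOF performance and number of practice members. So by the article's own account the extracted data can contain a clue. The questionnaire label is not one, because ten practices in every arm carry it.

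**Step 3: what one recognition exposes.** The ABE arm has 25 core practices, or 25 + 10 = 35 with the questionnaire practices. The totals are 3 × 25 = 75 and 3 × 35 = 105.

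| Practices counted | Exposed with a shared group code | Exposed without it |
|---|---|---|
| Core trial | 25 of 75 (33%) | 1 of 75 (1.3%) |
| With questionnaire practices | 35 of 105 (33%) | 1 of 105 (1.0%) |

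The other two arms stay indistinguishable from each other until a practice in one of them is recognised.

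**Step 4: how the chance accumulates (illustration).** The documents give no recognition probability. Assume that each ABE practice has an independent probability p of being recognised by someone who knows its allocation. The chance of at least one recognition among a practices is 1 − (1 − p)^a.

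| p | a = 25 | a = 35 |
|---|---|---|
| 1% | 22% | 30% |
| 2% | 40% | 51% |
| 5% | 72% | 83% |
| 10% | 93% | 98% |

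The table shows only that a small risk per practice becomes a sizeable risk for the arm once a group code is shared. It does not estimate what would happen in this trial.

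**Step 5: a route to recognition.** Year one and Appendix 1 compare each practice's audited prevalence with its QOF figure, so whoever prepares the feedback presumably has to tie an extract to a practice. That person also knows that the practice is in the ABE arm. Blinding explains unblinded staff only by mailing and invitations and does not mention preparing or presenting feedback. The article does not say who writes the feedback, whether they also work on the trial analysis, or whether the two files use the same practice pseudonyms.

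**The case against.** The strongest reply is that a masked group code with the key held elsewhere is a recognised form of analyst blinding, and that the article surrounds it with safeguards. The allocation database is separate, identifiers are pseudonymised, all arms are processed together, access to signature data is limited, and external CKD researchers have agreed to scrutinise the analysis procedures and results tables. The Discussion offers that scrutiny as the answer to the team's involvement with ABE. Who scripts feedback and when programs are locked are details that a condensed article may leave to a fuller document.

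Much of this stands, and it rules out several stronger readings that a reader might infer:

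- That the blind cannot hold. It can, if nobody in the analysis recognises a practice whose arm they know.
- That the grouping is in the table from the start. No timing is given, and a late addition would fit the text.
- That feedback and trial analysis share data files or staff. The article describes the same kind of source but states no shared file, pseudonym or person, and it says that analysts are not given the allocation.
- That interim results are seen by arm. No such comparison is described.
- That the ABE arm would reveal itself by moving first on proteinuria testing or angiotensin-modulating drugs. The guidelines arm has the same content and focus, so this is conjecture.

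What the reply leaves untouched is the arrangement that the article does state. None of the listed safeguards removes the group code. Limiting access to signature data is presented as an effort, not as an exclusion. The external scrutiny is not said to be blinded or to come before allocation is revealed.

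**Conclusion.** The concern holds in a limited form. The analyst blind is fragile as described, and the assurance that the data hold no clues conflicts with the article's own example of a signature and its own list of extracted fields. If a shared group code is present while derivation choices are still open, one recognised practice of known allocation exposes a third of the trial (25 of 75, or 35 of 105) instead of about 1%. ABE feedback is a possible route to that recognition which the blinding text does not address. Overlap between feedback and analysis is neither stated nor excluded.

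The conclusion rests on reading the grouping as a code shared by all practices in an arm, and on the code being visible before the derivation rules are fixed. The documents neither confirm nor deny the second condition. No bias in mmHg can be derived from them. The point justifies an inexpensive change to a stated arrangement. It does not show that the trial's result would be biased.

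**What to change.** - **Allocation concealment:** state that the working table carries no arm grouping, and no exact list size or similar signature field, until the cohort definition, cleaning rules, blood pressure selection rule and primary analysis program are locked. Have the external researchers named under Biomedical data check these under the existing scrutiny agreement, and merge the coded allocation only then.
- **Blinding:** state that staff who prepare or present ABE feedback take no part in those decisions, and that feedback extracts use practice pseudonyms different from those in the analysis table.
- **No-clues statement:** withdraw it, and say instead that re-identification is possible and how it is limited.

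The cost is small: a merge step later in the process and a second set of pseudonyms to maintain. Design, sample size and data collection are unaffected.
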